# A 2 × 2 factorial, randomised, open-label trial to determine the clinical and cost-effectiveness of hypertonic saline (HTS 6%) and carbocisteine for airway clearance versus usual care over 52 weeks in adults with bronchiectasis: a protocol for the CLEAR clinical trial

**DOI:** 10.1186/s13063-019-3766-9

**Published:** 2019-12-19

**Keywords:** Clinical trial protocol, Factorial design, Bronchiectasis, Hypertonic saline, Carbocisteine, Exacerbation, SWAT

## Abstract

**Background:**

Current guidelines for the management of bronchiectasis (BE) highlight the lack of evidence to recommend mucoactive agents, such as hypertonic saline (HTS) and carbocisteine, to aid sputum removal as part of standard care. We hypothesise that mucoactive agents (HTS or carbocisteine, or a combination) are effective in reducing exacerbations over a 52-week period, compared to usual care.

**Methods:**

This is a 52-week, 2 × 2 factorial, randomized, open-label trial to determine the clinical effectiveness and cost effectiveness of HTS 6% and carbocisteine for airway clearance versus usual care - the Clinical and cost-effectiveness of hypertonic saline (HTS 6%) and carbocisteine for airway clearance versus usual care (CLEAR) trial. Patients will be randomised to (1) standard care and twice-daily nebulised HTS (6%), (2) standard care and carbocisteine (750 mg three times per day until visit 3, reducing to 750 mg twice per day), (3) standard care and combination of twice-daily nebulised HTS and carbocisteine, or (4) standard care. The primary outcome is the mean number of exacerbations over 52 weeks. Key inclusion criteria are as follows: adults with a diagnosis of BE on computed tomography, BE as the primary respiratory diagnosis, and two or more pulmonary exacerbations in the last year requiring antibiotics and production of daily sputum.

**Discussion:**

This trial’s pragmatic research design avoids the significant costs associated with double-blind trials whilst optimising rigour in other areas of trial delivery. The CLEAR trial will provide evidence as to whether HTS, carbocisteine or both are effective and cost effective for patients with BE.

**Trial registration:**

EudraCT number: 2017-000664-14 (first entered in the database on 20 October 2017).

ISRCTN.com, ISRCTN89040295. Registered on 6 July/2018.

Funder: National Institute for Health Research, Health Technology Assessment Programme (15/100/01).

Sponsor: Belfast Health and Social Care Trust.

Ethics Reference Number: 17/NE/0339.

Protocol version: v3.0 Final_14052018.

## Background

### Background information

Bronchiectasis (BE) is a debilitating chronic illness caused by irreversible dilatation, thickening and sac-like formations in bronchial walls. Patients usually suffer from a persistent cough, chronic daily sputum expectoration, recurrent chest infections and poor health-related quality of life (HRQoL) [1, 2]. Current estimates suggest around 5 in 1000 people in the UK have BE [3, 4] with higher numbers of patients being diagnosed with BE due to increased use of high-resolution computed tomography (HRCT) [5]. Mortality in the 52 weeks after a BE-related exacerbation is as high as 30% [6]. Morbidity is also high and UK hospitals admission data indicate that BE was the primary diagnosis in 1 in 1800 admissions, with a sevenfold increase in hospital bed days needed for treating BE in the first decade of the 21st century [7, 8].

Mucus hypersecretion is a clinical feature of BE. Airway mucosal infection often gives rise to inflammatory mediators [9], including neutrophil-derived DNA and filamentous actin, in addition to apoptotic cells and cellular debris that may collectively increase mucus production and viscosity. This mucus retention aids bacterial infection that can lead to pulmonary exacerbations, which further develops the “viscous cycle” of mucus retention, infection, inflammation and tissue damage [10]. Mucoactive drugs target this cycle by potentially increasing the ability to expectorate sputum and/or decrease mucus hypersecretion. Mucoactive drugs are classified in terms of their proposed primary mechanism of action: expectorants induce mucus expulsion, mucoregulators reduce mucus secretion, mucolytics decrease viscosity and mucokinetics increase cilia activity.

### Rationale for the study

The current guidelines indicate that mucoactive drugs plus airway clearance may be considered to enhance sputum expectoration in BE [11, 12] but Cochrane reviews have shown that the evidence to support their use is limited. Recent reviews have demonstrated that DNase and mannitol do not reduce exacerbations [13, 14]. In clinical trials, DNase increased exacerbations and resulted in a significant decrease in lung function [15]. And, as shown in a recent overview of reviews, evidence for the effectiveness of hypertonic saline (HTS) and carbocisteine is insufficient to recommend them within the management of BE [16]. However, European Multicentre Bronchiectasis Audit and Research Collaboration (EMBARC)/UK Bronchiectasis Registry (BRONCH-UK) data show that BE centres do prescribe mucoactive drugs. This is important because adherence to therapy in BE in general is low and decreases as the number of prescribed medications increases, and is also related to poorer patient outcomes, including the number of pulmonary exacerbations and quality of life [17]. Therefore, it is essential that only those drugs that are effective should be prescribed for patients with BE. There are cost considerations associated with mucoactive drugs, and there is a risk of polypharmacy side effects.

### Rationale for the interventions (use of HTS and carbocisteine)

The physiological rationale for the use of HTS in BE is based on its osmotic effects on the airway surface layer that improves airway hydration and accelerates mucus transportability, especially when combined with airway clearance techniques (ACT). There have been multiple, crossover studies exploring the use of HTS in BE [18–21] that support these effects. The only long-term (1 year) randomised, parallel-group study did not demonstrate long-term efficacy of HTS (6%) compared to placebo [22], but this “no effect” result may have been due to poor study design or lack of power, the way in which exacerbation data were collected, a true lack of effect of HTS on mucus clearance or due to chance. Thus, the need to explore the use of HTS in BE remains, and patients and practitioners need to have these important uncertainties resolved. The physiological rationale for carbocisteine is based on its ability to reduce the concentration of mucus glycoprotein, which reduces the viscosity of mucus and facilitates expectoration. As with HTS, the evidence base for carbocisteine in BE is poor. This contrasts to other respiratory conditions, where there is relatively strong evidence favouring both HTS and carbocisteine [22–24]. Therefore, the CLEAR trial will answer important clinical questions about whether similar benefits can be demonstrated in BE by using a pragmatic design to explore the specific effects of mucoactive agents, and directly support, or refute, more targeted use of these drugs.

### Rationale for comparator

In the CLEAR trial, the comparator will be standard care. In the UK, standard care is defined by the British Thoracic Society (BTS) guidelines for BE [25]. All sites will be encouraged to follow these guidelines such that all patients in the control group (as well as in the three intervention groups) will be expected to have been prescribed and taught ACT. If patients are not familiar with ACT, they will be taught the active cycle of breathing techniques [26].

### Objectives

The primary objective of the CLEAR trial is to determine whether HTS (6%) and/or carbocisteine reduces the mean number of exacerbations over 52 weeks. Secondary objectives are to determine whether HTS and/or carbocisteine improve disease-specific HRQoL, reduce time to next exacerbation, reduce number of days of antibiotics for treatment of exacerbations, improve generic HRQoL, are acceptable from a patient satisfaction perspective, are associated with adverse events (AEs) and improve lung function over 52 weeks. The study will also assess cost effectiveness and treatment adherence.

### Study design

CLEAR is a multicentre, superiority, 2 × 2 factorial, randomized, open-label trial in BE with a 52-week follow-up period. Patients will be randomised (1:1:1:1 ratio) to one of four groups: HTS alone, carbocisteine alone, HTS and carbocisteine or standard care. Additionally, all patients will be followed up at 104 weeks to explore their mucoactive drug use in the 52 weeks following the completion of the main trial. For the SPIRIT checklist, please see Additional file 8.

### Embedded sub-studies

There are three embedded sub-studies within the CLEAR trial. The first aims to validate and measure the sensitivity of the EMBARC definition of exacerbations in BE (see Additional file 1). The second sub-study will examine the use of a new home spirometer *my*SpiroSense for remote monitoring (see Additional file 3). The third will use Studies Within A Trial (SWAT) [27] to explore the effect of methods used to optimise recruitment and retention (see Additional file 4). These sub-studies will be reported separately from the main report for CLEAR.

## Methods/design

### Study setting

The CLEAR sites will include at least 16 National Health Service (NHS) hospitals in the UK with access to patients with BE managed according to BTS guidelines. Sites will include those that are part of the BRONCH-UK/or EMBARC research network [28], and additional sites will be chosen from the Northern Ireland Clinical research Network (NICRN)/National Institute for Health Research Clinical Research Network (NIHR CRN) portfolio if required. The current list of study sites is in Additional file 5.

### Internal pilot study

The main trial will be preceded by an 8-month internal pilot study in 10 sites, which will follow the processes described for the main trial with target recruitment of 60 patients. This internal pilot will be used to confirm recruitment rates, protocol compliance and data collection methods.

### Characteristics of participants

Patients will be eligible to participate in the CLEAR trial if they fulfil the following inclusion criteria: diagnosis of BE on computerised tomography (CT)/HRCT, BE as the primary respiratory diagnosis, two or more pulmonary exacerbations in the last year requiring antibiotics (including patient-reported exacerbations), production of daily sputum, stable for 14 or more days before first study visit with no changes to treatment, willing to continue any other existing medication for chronic illness throughout the study, and female participants must be either surgically sterile, postmenopausal or agree to use effective contraception during the treatment period of the trial.

The exclusion criteria are as follows: < 18 years old, cystic fibrosis (CF), chronic obstructive pulmonary disease (COPD), current smokers, female ex-smokers with > 20 pack years and male ex-smokers with > 25 pack years, forced expiratory volume in 1 s (FEV_1_) < 30%, if being treated with long term macrolides on treatment for < 1 month before joining study, regular isotonic saline, HTS, carbocisteine or any mucoactive drugs taken within the past 30 days, known intolerance or contraindication to HTS or carbocisteine, contraindications to or special warnings against the use of carbocisteine (active peptic ulceration, hereditary galactose intolerance, Lapp-lactase deficiency, glucose-galactose malabsorption), unable to swallow oral capsules, women who are pregnant or lactating, or participation in another clinical trial of an investigational medicinal product (IMP) within 30 days. Patients currently using mucoactive drugs can be considered for the CLEAR trial if they stop these for at least 30 days before being assessed for eligibility.

### Screening and informed consent

Written informed consent will be obtained by the site principal investigator or appropriately trained designee. All interested individuals who are eligible using the screening criteria will be given a participant information sheet and allowed as much time as necessary to consider the study. Informed consent will be obtained using standard procedures (Additional files 6 and 7).

### Intervention and comparator

The interventions and comparators are as follows:
Intervention 1: standard care and twice-daily nebulised HTS (MucoClear 6%, PARI Pharma GmbH). Participants will be instructed to administer a 1 × 4 mL ampoule twice daily for 52 weeks using the eFlow rapid nebuliser and eTrack controller (PARI Pharma GmbH).Intervention 2: standard care and carbocisteine (750 mg three times per day until visit 3*, reducing to 750 mg two times per day) over 52 weeks.Intervention 3: standard care and combination of twice-daily nebulised HTS (MucoClear 6%, PARI Pharma GmbH). Participants will be instructed to administer a 1 × 4 mL ampoule twice daily for 52 weeks using the eFlow rapid nebuliser eFlow rapid nebuliser and eTrack controller (PARI Pharma GmbH). They will also be given carbocisteine (750 mg three times per day until visit 3*, reducing to 750 mg twice per day) over 52 weeks.Comparator: standard care over 52 weeks. Patients in the standard care group will use airway clearance techniques in the management of their BE.

*Visit 3 occurs 8 weeks (±7 days) after the baseline assessment).

### Concomitant care

Sites in this study all follow BTS guidelines for management of BE. Any prescribed medication deemed necessary to provide adequate medical care to the patient is permitted, other than as stated in the study exclusion criteria. The use of mucoactive drugs/isotonic saline outside the allocated treatment is not permitted except for short periods during exacerbations.

### Treatment discontinuation

All patients allocated to a treatment group including HTS 6% will complete a drug response assessment prior to commencing HTS in accordance with a study-specific guideline and if they do not pass this they will not continue on the study. Participants may withdraw from treatment at any time, without providing an explanation, or if discontinuation is considered by the medical team to be in the best interests of the patient. Anticipated reasons for withdrawal include intercurrent significant illness, occurrence of intolerable side effects, patient request, protocol violations or decision that the study drug should be discontinued on safety grounds. A participant may be withdrawn from the study at the discretion of the Investigator due to safety concerns.

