### Randomisation and blinding

Treatment allocation at each site will be assigned using a concealed automated randomisation process provided by an external organisation. Participants who give their consent will be allocated using a fixed block size to one of the four groups (three intervention groups or one standard care group) in a 1:1:1:1 ratio using a central randomisation system. Randomisation will be stratified by (1) site, (2) exacerbations in the last year (2–3 times, > 3 times) (to minimise baseline imbalances in antibiotic use) and (3) current use of macrolides (yes, no). The trial is open label, and patients, investigators and outcome assessors will be aware of treatment allocation.

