### Data collection, quality and procedures

All data collected during study visits and telephone calls with each patient will be recorded in the CLEAR source documents/electronic case report form (CRF). If a participant withdraws during their first year on the study, they will be asked to attend follow-up visits for collection of outcome data. If they do not wish to attend outcome data collection, permission will be sought to access medical notes for collection of data relevant to the trial e.g. the use of antibiotics. If a participant withdraws from all parts of the study, their anonymised data (recorded up to the point of withdrawal) will be included in the study analysis. All patient data will be anonymised.

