### Statistical analysis

Baseline characteristics, follow-up measurements and safety data will be described using descriptive summary measures depending on the scale of measurement. The primary analysis will be conducted on a modified intention-to-treat basis consisting of randomised participants with data from at least one post-baseline efficacy assessment. A per-protocol analysis may also be conducted to compare treatment groups. Groups will be compared for the primary outcome (number of exacerbations over 52 weeks) and antibiotic use (number of days of antibiotic use over 52 weeks) using negative binomial regression adjusted for baseline characteristics and other covariates. The QoL-B and other continuous outcomes will be compared between groups using analysis of covariance (ANCOVA) adjusting for baseline characteristics and other covariates. The trial’s 2 × 2 factorial design permits the separate testing of the effects of HTS and carbocisteine on HRQoL and the detection of any interaction between them. These tests will be implemented using three contrasts (representing HTS, carbocisteine and the interaction) in the models. For time to next exacerbation, Kaplan-Meier curves will be prepared and the log-rank test applied to compare the groups. Analyses will be two-sided and tested at an a priori significance level of *p* = 0.05. The primary time point has been defined as 52 weeks after randomisation. There is no adjustment for multiple testing at the different time points, because the primary outcome has been pre-defined and prioritised. Standard approaches will be used to detect missing data.

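### Patients who fail a drug response assessment taken only after allocation to HTS are said to leave the study, and the protocol does not say whether they are still followed up and analysed as randomised

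*Protocol article*

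**What the plan says.** Three sections of the protocol article bear on this.

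- **Treatment discontinuation.** The assessment follows allocation and applies to the HTS groups only: "All patients allocated to a treatment group including HTS 6% will complete a drug response assessment prior to commencing HTS". For those who fail, "if they do not pass this they will not continue on the study". Elsewhere the same section distinguishes withdrawal from treatment from withdrawal from the study.
- **Statistical analysis.** The primary analysis is on a "modified intention-to-treat basis consisting of randomised participants with data from at least one post-baseline efficacy assessment". The drug response result is not mentioned.
- **Data collection, quality and procedures.** "If a participant withdraws during their first year on the study, they will be asked to attend follow-up visits for collection of outcome data". Where visits are declined, permission is sought to use their medical notes. For anyone who leaves every part of the study, "their anonymised data (recorded up to the point of withdrawal) will be included in the study analysis".

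Before randomisation, the eligibility criteria exclude "known intolerance or contraindication to HTS or carbocisteine". They list no tolerance test, so an intolerance first found at the assessment comes to light after allocation.

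**The concern.** Randomisation makes the HTS and non-HTS margins comparable only if patients are kept or lost by the same rule on both sides. Here one rule operates on one side. A patient who would have failed the assessment leaves if allocated to HTS, but stays if allocated to carbocisteine alone or standard care.

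Someone who leaves before the first HTS dose would normally have no efficacy data after baseline, and so would not meet the definition of the primary set. The comparison would then be between HTS patients who passed and an unselected non-HTS group. If passing is related to exacerbation risk, the HTS contrast is biased, and a larger sample would not remove the bias. The effect of HTS on exacerbations is part of the primary objective. Outcomes that were never collected cannot be recovered by a statistical analysis plan.

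**Working it through.** **1. The planned numbers.** Sample size section: SD 0.9, difference 0.4, 90% power, two-sided 5%. Per group, n = 2 × (1.960 + 1.282)² × 0.9² / 0.4² ≈ 106.4, so 107, or 214 in total (stated: 216). Then 216 × 1.5 = 324, and 324 / 0.85 ≈ 382 (stated: 380). The figures reproduce within rounding. With 95 per group, 190 are allocated to HTS and 190 are not.

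**2. The follow-up rule, read both ways.**

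| Reading | Patients who fail | HTS contrast |
|---|---|---|
| Treatment discontinuation section taken literally | Leave before the first HTS dose, normally with no efficacy data after baseline, so outside the primary set | Those who passed versus everyone |
| Withdrawal provisions also cover them | Asked to attend visits, or notes used with permission, so can enter the primary set | Preserved as randomised |

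The article does not say which is meant.

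**3. Illustration under the literal reading.** Let a share f of patients fail, and let them have r times the exacerbation rate of the others. Neither f nor r is given, so both are assumptions. With no true HTS effect, the non-HTS side has mean rate proportional to 1 − f + f·r and the retained HTS side to 1. The expected rate ratio is therefore 1 / (1 − f + f·r).

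To express this as a difference, take the planning mean of 0.7: the apparent difference is 0.7 × (1 − rate ratio). The two-sided type I error uses a normal approximation with SD 0.9 and 15% ordinary dropout, so n = 190 × 0.85 = 161.5 without HTS and 161.5 × (1 − f) with HTS.

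| f | r | Lost of 190 | Rate ratio | Apparent difference (share of 0.4) | Type I error |
|---|---|---|---|---|---|
| 5% | 1.5 | about 10 | 1/1.025 = 0.98 | 0.017 (4%) | 5.3% |
| 10% | 2 | 19 | 1/1.10 = 0.91 | 0.064 (16%) | 9.5% |
| 15% | 2 | about 29 | 1/1.15 = 0.87 | 0.091 (23%) | 14% |
| any | 1 | 190f | 1 | 0 | 5% |

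If those who fail had the lower risk, the sign would reverse: f = 10% and r = 0.5 gives 1/0.95 = 1.05.

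**4. Power.** For a true difference of 0.4, losing 2% to 15% of the HTS side leaves power at 97.8% to 96.9%, against 97.9% with 162 per margin. The issue is possible bias, not precision.

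**5. The other contrasts.** Carbocisteine is compared within each HTS level. If failing does not depend on carbocisteine allocation, that contrast is largely protected and the cost is mainly lost data. The interaction is built from the same selected HTS groups. On the ratio scale the factor 1 / (1 − f + f·r) cancels from it only if f and r are the same with and without carbocisteine.

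**The case against.** The strongest reply is that exclusion from the primary analysis is inferred, not stated. The analysis section admits any randomised participant with efficacy data after baseline, and the withdrawal provisions are broad enough to include patients who fail. The sentence sits under a heading about stopping treatment, so loose wording is possible. It also defers to a trial-specific guideline that is not shown, and the schedule table is missing. This stands to the extent that the loss cannot be asserted as fact. It does not remove the point: the literal wording says study, in a section that elsewhere distinguishes study from treatment, and the withdrawal provisions never mention these patients. Sites could follow either section.

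A reader might go further and infer that the exclusion makes HTS look better, on the view that patients who react to inhaled saline have worse disease. The document links failing to exacerbation risk nowhere. The existing exclusions for known intolerance, COPD and FEV1 below 30% may also keep the failure rate low.

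More alarming error rates can be produced. One extra exacerbation a year in those who fail gives type I error of about 16% at f = 10% and 30% at f = 15%. With an overall mean of 0.7, however, that excess implies r of 1.6/0.6 ≈ 2.7 and 1.55/0.55 ≈ 2.8, and nothing in the article supports ratios of that size.

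Nor does the text support a claim that the carbocisteine comparison is compromised in the same way.

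**Conclusion.** The point holds as a conflict over follow-up with a possible effect on a primary contrast. Read literally, the protocol removes patients after randomisation from the HTS side only. Combined with the definition of the primary set, the HTS main effect and the interaction would then not compare the groups as randomised. If the withdrawal provisions are meant to apply and are followed, the HTS comparison is preserved. The article does not settle which.

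The direction and size of any bias are unknown. The illustrative rate ratios of 0.98 to 0.87 rest wholly on assumed f and r and on the literal reading. The bias is negligible if few fail, and zero if failing is unrelated to prognosis.

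**What to change.** Leave the clinical rule on starting HTS as it is. Reconcile the Treatment discontinuation and the Data collection, quality and procedures sections by stating that patients who fail the assessment:

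- remain in outcome follow-up under the existing withdrawal provisions (visits, or notes with permission); and
- are analysed in the group to which they were randomised, so that membership of the primary set does not depend on the assessment result.

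No new definition of the analysis set is needed once follow-up is kept. What happens to carbocisteine in combination-group patients who fail is a clinical matter for the sponsor to clarify.

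The cost is wording, follow-up of a small number of non-starters by existing procedures, and some dilution of the HTS estimate. If 0.4 is the effect in those who start HTS and non-starters gain nothing, the expected difference is 0.4 × (1 − f): 0.38, 0.36 or 0.34 for f of 5%, 10% or 15%. With 162 per margin the standard error is 0.9 × √(2/162) = 0.10, so power is about 97%, 95% or 93%, still above the planned 90%.

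The Trial status section reports 130 recruited of the planned 380, so the clarification could still cover the remaining 250. For any earlier patients who failed, access to notes with permission may recover the outcome.
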